# Pragmatic controlled trial of a school-based emotion literacy program for 8- to 10-year-old children: study protocol

**DOI:** 10.1186/s12888-024-05628-z

**Published:** 2024-04-12

**Keywords:** Mental health, Health literacy, Child & adolescent psychiatry, Schools, Health education

## Abstract

**Background:**

Mental disorders are common in childhood, but many young people do not receive adequate professional support. Help-seeking interventions may bridge this treatment gap, however, there is limited research on interventions for primary-school children. This study aims to evaluate the effectiveness of an emotion literacy program at increasing literacy, reducing stigma, and promoting help-seeking in children aged 8–10 years.

**Methods and analysis:**

A two-arm pragmatic cluster-controlled trial will compare Thriving Minds, an emotion literacy program for middle primary school children, to a wait-list control condition. Children aged 8–10 years will be recruited from approximately 12 schools (6 intervention schools/6 wait-list control) to participate in Thriving Minds via direct invitation by the program delivery service. Allocation to the intervention condition will be pragmatically, by school. Children will receive the intervention over two 50-minute sessions, across two weeks. Using story books and interactive discussion, the program aims to develop children’s knowledge of their own and other’s emotional experiences and emotion regulation strategies (self-care and help-seeking). The primary outcome is help-seeking intentions. Secondary outcomes include help-seeking knowledge, attitudes, and behaviours, emotion knowledge and attitudes, and stigma. Children will complete surveys at pre-intervention, post-intervention (one week after the program) and 12-week follow-up. Additional satisfaction data will be collected from teachers in intervention schools via surveys (post-intervention and 3-month follow-up) and semi-structured interviews (after follow-up), and selected children via focus groups (12-week follow-up). Analyses will compare changes in help-seeking intentions relative to the waitlist control condition using mixed-model repeated-measures analyses to account for clustering within schools.

**Discussion:**

With demonstrated effectiveness, this universal emotion literacy program for promoting help-seeking for mental health could be more widely delivered in Australian primary schools, providing a valuable new resource, contributing to the mental health of young people by improving help-seeking for early mental health difficulties.

**Trial registration:**

Australian New Zealand Clinical Trials Registry, ACTRN12623000910606 Registered on 24 August 2023.

**Supplementary Information:**

The online version contains supplementary material available at 10.1186/s12888-024-05628-z.

## Introduction

Early access to mental health services and support is critical, as untreated mental disorders can significantly affect a child’s social, emotional and academic functioning, both in the short and long term [1]. Research suggests, however, that many young people do not readily seek or receive treatment or support for psychological distress or mental disorders [2, 3]. A recent systematic review and meta-analysis of the prevalence of mental disorders in children and adolescents in high-income countries found that only 44.2% of young people with mental disorders received any services for their conditions [2]. Another study conducted in Australia reported slightly higher rates of service use among children and adolescents, with 56.0% accessing services for emotional and behavioural problems [3].

Several barriers to help-seeking have been identified, including limited mental health knowledge (literacy), perceived social stigma and embarrassment, low perceived confidentiality and trust in mental health service providers, financial costs, logistical barriers, and limited availability of services [1]. Mental health knowledge and stigma are two modifiable factors that could be readily targeted in a low-intensity intervention to improve help-seeking in children. Schools have been identified as the ideal setting in which to implement mental health prevention programs including mental health literacy interventions, as they have unprecedented contact with children, and may be more likely to reach young people from marginalised backgrounds who often experience higher rates of mental disorders [4]. Indeed, some schools implement whole-school mental health prevention programs that may include elements of mental health literacy (e.g., KidsMatter [5]), with studies suggesting that these comprehensive programs can have positive effects on children’s mental health [6, 7]. We know less about brief, standalone mental health literacy interventions designed to facilitate help-seeking and reduce stigma, particularly for younger children.

To date, a number of studies have been conducted in schools to assess the effectiveness of brief interventions specifically designed to increase mental health literacy to improve help-seeking, and/or reduce stigma. A recent review of such interventions identified significant positive effects on knowledge and awareness of mental disorders in 86% of studies, and more positive attitudes and beliefs regarding mental disorders observed in 56% of studies [4]. Of the 22 randomised controlled trials (RCTs) identified in the review, only two were conducted with primary school (elementary) aged children.

The lack of rigorous research on mental health literacy programs in primary school aged children suggests an area of significant unmet need, particularly given evidence that mental health stigma can develop early [8, 9]. As such, educating children about mental health before their conceptualisations are fully formed may assist in preventing the formation of negative attitudes and foster more accurate knowledge and awareness of their own and other people’s mental health [10]. The two interventions delivered in primary schools that were identified in our review [11, 12] both targeted mental health stigma and reported positive effects on knowledge, attitudes and social distance. These studies were limited to the northern hemisphere, and only one was controlled with follow-up [11].

One of the challenges associated with delivering mental health literacy programs in primary school settings is that primary school age children have varying and emerging levels of emotion literacy, which is a prerequisite to mental health literacy. Jorm et al. [13] defined mental health literacy as “the knowledge and beliefs about mental health problems that help in their recognition, management, and prevention.” Here, drawing from literature on emotion understanding, we define *emotion literacy* as children’s conceptual knowledge and understanding of emotional experiences (including context, causes, physiological reactions, cognitions, and behaviours), and actions or responses that support regulation [14–16]. Lower emotion literacy is related to children experiencing anxiety, depression, and behavioural issues [17–19]. Emotion literacy is one of the main components of emotion competence [20, 21] and therefore a foundational part of mental health literacy. Understanding and differentiating between emotional experiences contributes to the ability to choose appropriate regulation strategies, including help-seeking.

Although children often require adult assistance to seek help, providing them with the capability to identify their experiences, knowledge of available supports, and the ability to destigmatise difficult emotional experiences, may facilitate direct help-seeking behaviour (e.g., through school psychologists) and indirect help-seeking (e.g., by giving them the language to tell a trusted adult about their mental health experiences). One newly established brief intervention promoting these skills is the Thriving Minds program for 8-10-year-olds [22]. Through story books and interactive discussion, the program aims to develop children’s knowledge of their own and other’s emotional experiences and emotion regulation strategies of self-care and help-seeking. The middle primary age group was chosen because it reflects a stage of childhood emotion development by which basic emotion knowledge has usually been established [23, 24]. From about 8 years old, children are developing a more complex understanding and knowledge of emotions, increasing their emotion regulation strategies, and learning about the moral components of emotion [14, 23, 24]. By early adolescence, children have developed an increasing awareness of social expectations of peers and others, enabling the awareness and endorsement of stigma about mental health; such stigma prevents help-seeking [25]. Given that stigma prevents help-seeking, middle primary years may be an ideal target age for interventions focusing on early de-stigmatisation and help-seeking for emotional experiences.

An uncontrolled post-program evaluation of the Thriving Minds program with two schools found a high level of satisfaction and engagement with the program, with 89% of students rating it 4.54 (*SD* = 0.76) stars out of 5. At the 6–8-week follow-up, over 85% of participants reported that they knew where to go to for help for difficult emotions [26]. The proposed multi-site pragmatic controlled trial will provide a more rigorous evaluation of the program in a broader sample of schools.

### Aims and hypotheses

Using a pragmatic cluster-controlled trial, this study will investigate the efficacy of a school-based mental health literacy program for 8-10-year-old children. The primary aim of the trial is to evaluate the effect of the Thriving Minds program on help-seeking intentions for uncomfortable emotions at post-intervention (and, secondarily, 12-week follow-up), compared to the wait-list control condition. It is hypothesised that participants receiving the Thriving Minds program, relative to participants in the wait-list control condition, will report higher levels of help-seeking intentions for uncomfortable emotions at post-intervention.

The secondary aims are to evaluate at post-test and 12 week follow-up the following: 1) the efficacy of Thriving Minds on a range of help-seeking outcomes: (a) help-seeking confidence, b) help-seeking knowledge, c) help-seeking attitudes, d) actual self-care behaviours, and e) actual help-seeking behaviours; 2) the effect of Thriving Minds on emotion knowledge ((a) emotion recognition and (b) physiological components of emotion); and 3) the effect of Thriving Minds on stigma. It is hypothesised that participants receiving Thriving Minds will report improvements in each of these outcomes relative to the waitlist control.

Exploratory aims include exploring *Predictors and mediators* of intervention effects, including demographic characteristics, mental health conditions, emotion knowledge (emotion vocabulary, and bodily awareness of emotions) and emotion stigma (emotion attitudes (not hiding emotions)), wellbeing, and school support. These analyses will also investigate subgroup effects, such as whether the Thriving Minds program has a greater effect on emotion knowledge among students with low pre-existing knowledge.

A final aim of the study is to conduct a qualitative evaluation to assess *student and staff satisfaction* with the program, including what students liked and learned in the program, any suggested improvements, and any observable changes in student learning, behaviour or wellbeing following the intervention.

## Methods and analysis

### Study design

This study protocol complies with the SPIRIT guidelines (Supplementary Materials B). A pragmatic controlled cluster trial will be conducted in at least 12 primary schools (6 intervention condition/6 wait-list control condition) with three measurement occasions (pre-intervention, post-intervention and 12-week follow-up). Surveys for participating classroom teachers will be delivered at post-intervention and 12-week follow-up. A qualitative evaluation will also be conducted through open-ended survey items for students at post-intervention, focus groups with selected children, and semi-structured interviews with selected staff from intervention condition schools after the12-week follow-up assessment.

### Participants and recruitment

We will recruit approximately 500 8- to 10-year-old students in total, drawn from at least 12 schools in the Australian Capital Territory (ACT). Based on a previous primary school RCT of a mental illness stigma intervention [11], we anticipate an effect size of *d* = 0.35 in literacy and stigma. Based on typical session sizes of *n* = 40–50 students per school, recruiting at least 12 schools (6 intervention/6 control; N = approx. 500) will provide > 83% power to detect an effect, assuming up to 20% attrition and accounting for clustering with an intraclass correlation of 0.03. Schools will be recruited via pre-existing relationships with the intervention provider, MIEACT. All children in participating school year groups will be eligible to participate, pending parental consent. Information and consent forms will be distributed by classroom teachers to students and their parent/guardian prior to the trial commencing. Children with parental consent will also receive study information and provide written consent at the time of their first survey and will assent via survey completion for subsequent surveys. All participants will have access to information on crisis support numbers and mental health websites for use if they are feeling distressed. This information will be included on the information sheet provided to participants and their parents/caregivers, as well as at the end of each survey.

Usual teachers of participating students will be asked to complete a brief survey at post-intervention and 12-week follow-up timepoints (*n* = approximately 30). We aim to also invite between one and three school staff per intervention school to participate in a semi-structured interview after the 12-week follow-up survey. The staff members targeted for interviews will be Executive staff holding key pastoral care positions and classroom teachers.

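### The stated power of more than 83% does not follow from the inputs listed with it, which give about 70% or 61% for a two-sided 5% post-intervention comparison; reaching 83% needs an undeclared input

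*Protocol article*

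**What the plan says.** The only sample-size justification is in the protocol article under Participants and recruitment. Its inputs are:

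- Effect: "we anticipate an effect size of *d* = 0.35 in literacy and stigma".
- Clusters and total: "recruiting at least 12 schools (6 intervention/6 control; N = approx. 500".
- Cluster size: "typical session sizes of *n* = 40–50 students per school".
- Loss: "assuming up to 20% attrition".
- Clustering: "accounting for clustering with an intraclass correlation of 0.03".

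The conclusion is that this gives more than "83% power to detect an effect, assuming up to 20% attrition and accounting for clustering with an intraclass correlation of 0.03". The paragraph gives no significance level, sidedness, pre-post correlation or degrees-of-freedom method. It does not say whether the figure refers to one time point or to the repeated-measures model. The Data analysis plan specifies a mixed-model repeated-measures analysis with random school effects, with occasion as the within-group factor and condition as the between-groups factor. The pre-intervention survey is one of the three occasions.

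**The concern.** A reader who puts the five listed inputs into the standard cluster-trial formula does not get 83%, and the gap is far beyond rounding. Nothing else in the article justifies the number of schools. If the figure is too high, the risk of missing a true d of 0.35 is larger than the 17% implied, and a null result could be over-read as evidence that the program does not work. If it is right, it rests on an assumption that the reader cannot see or judge.

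**Working it through.** **Inputs from the article:** d = 0.35 (SD = 1); N = 500; 12 schools; 20% attrition; ICC = 0.03. The article gives the effect for literacy and stigma; it is used here as stated. **Assumed, because not stated:** 5% significance level, two-sided, comparison at post-intervention only. Variations follow.

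**Attempt to reproduce the stated figure**

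- Analysed: 500 × 0.8 = 400, or 200 per arm and 400 / 12 = 33.3 per school.
- Design effect = 1 + (m − 1) × ICC = 1 + 32.33 × 0.03 = 1.97.
- Effective n per arm = 200 / 1.97 = 101.5.
- SE(d) = √(2 / 101.5) = 0.1404.
- Noncentrality = 0.35 / 0.1404 = 2.494.
- Normal approximation: Φ(2.494 − 1.96) = 70.3%.
- Noncentral t with 12 − 2 = 10 df: 61.4%.

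The stated figure is not reproduced.

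**More generous two-sided readings, same ICC, no baseline correlation**

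| Enrolled | Attrition | Normal | t, 10 df |
|---|---|---|---|
| 480 | 20% | 69.4% | 60.6% |
| 500 | 20% | 70.3% | 61.4% |
| 600 | 20% | 74.0% | 65.1% |
| 500 | none | 74.7% | 65.9% |
| 600 | none | 77.9% | 69.1% |

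The top of the 40–50 range with no loss at all still falls about 5 points short of 83%.

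**One-sided 5%**

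- 500 enrolled, 20% lost: 80.2% (normal), 75.0% (t).
- 600 enrolled, 20% lost, or 480 enrolled, none lost: 83.1% (normal), 78.1% (t).
- 500 enrolled, none lost: 83.7% (normal), 78.8% (t).

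**Using the pre-intervention survey (N = 500, 20% attrition, two-sided)**

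For 83% power the noncentrality must be 1.96 + 0.954 = 2.914 (normal) or 3.236 (t, 10 df). The same design effect is kept throughout.

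- Baseline as covariate, variance factor 1 − ρ²: ρ = √(1 − (2.494 / 2.914)²) = 0.52 (normal); √(1 − (2.494 / 3.236)²) = 0.64 (10 df). At ρ = 0.5 power is 82.1% (normal) or 73.8% (t). At ρ = 0.6 it is 87.6% or 80.2%.
- Change contrast, variance factor 2(1 − ρ): ρ = 1 − (2.494 / 2.914)² / 2 = 0.634 (normal), so 0.64 is enough to clear 83%. With 10 df, 1 − (2.494 / 3.236)² / 2 = 0.70. At ρ = 0.5 the factor is 1, so there is no gain over the post-only comparison (70.3%). At ρ = 0.4 power falls to 62.4% (normal).

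**Detectable effect at 80% power, two-sided, post-only**

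- Normal: (1.96 + 0.842) × 0.1404 = 0.39.
- t, 10 df: 3.110 × 0.1404 = 0.44.

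**The case against.** The best defence is that 61–70% describes a test the trial does not plan. The significance level, the two-sided test and the absence of any benefit from baseline are supplied here, not by the article. The planned model includes the pre-intervention occasion, and a pre-post correlation of about 0.52 is an ordinary size of assumption. A condensed article may also leave the formula, sidedness and correlation to a fuller document, and 12 schools is a minimum ("recruiting at least 12 schools (6 intervention/6 control").

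Much of this stands. A reader might infer that the trial's true power is only 61–70%, or that the risk of missing d = 0.35 is 30–39%. The article does not support that, because those figures belong to the post-only two-sided comparison. The 10-df value also presumes a small-sample method that the article neither adopts nor rejects.

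What does not stand is the sentence itself. It publishes a specific figure beside a specific list of assumptions, and the list does not yield the figure. That is a mismatch in what is stated, not a detail left elsewhere. The correlation needed also depends on how baseline enters the model: 0.52 suffices as a covariate on the normal approximation, but a change contrast or 10 df needs about 0.64, and both together about 0.70. The article gives no correlation for the primary measure.

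The one-sided route does not rescue the sentence either. It reaches 83.1% only with 600 enrolled, which conflicts with about 500, or with no attrition, which conflicts with the 20% allowance. A directional hypothesis is not a declared one-sided test.

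**Conclusion.** The stated power of more than 83% is not delivered by the inputs given for it. On those inputs a two-sided 5% comparison at post-intervention has about 70% power (normal) or 61% (t, 10 df), a shortfall of roughly 13 to 22 points. No two-sided reading of the stated ranges without a baseline correlation exceeds 78%. The figure can be reached only through an undeclared pre-post correlation, or a one-sided test combined with a larger sample or no loss. The power of the planned repeated-measures model is unknown from the article and may be above or below 83%. The arithmetic is firm. The 61–70% range depends on the assumed 5% two-sided level and on no use of baseline.

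**What to change.** Take one of two routes in Participants and recruitment.

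1. Restate the power on the listed inputs as about 70% (about 61% with 10 between-school df), or give the detectable effect as d of about 0.39 to 0.44 at 80% power. Label either one as a two-sided 5% post-only comparison, so that it is not read as the power of the planned model.
2. If 83% relied on the repeated-measures model, state the significance level, sidedness, assumed pre-post correlation and degrees-of-freedom method. Then recompute the power for that model at 500 enrolled with 20% attrition, over a range of correlations.

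Either route costs a sentence or two and possibly a less favourable figure. No extra recruitment is needed.

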### Condition allocation

Allocation of schools to the trial conditions (intervention or wait-list control) will be on a pragmatic basis, due to the limited flexibility in school timetables. Where possible, schools will be matched across conditions based on school type (public vs. private) and socioeconomic status, with at least six schools per condition. Using a predetermined schedule accounting for program delivery staff availability, MIEACT will provide schools with a choice of available times in which Thriving Minds could be delivered and schools will nominate feasible options based on timetable and curriculum planning. School nominations will contribute to their allocation to the intervention or control condition (e.g., schools who choose early year program delivery will need to be intervention schools, due to insufficient lead time for control condition surveys). Parents will be sent consent forms with random, unique participant ID numbers so that signing a consent form allocates each child a participant ID number, which will also allow the linking of parent provided child mental health information to each child.

### Procedure

To facilitate recruitment and intervention delivery, the trial will be conducted over at least two school years (Terms 3 and 4, 2023 and Terms 1 and 2, 2024). All consenting students will be invited to complete a pre-intervention survey one week prior to the intervention condition schools receiving the Thriving Minds program. The program will be delivered to all students in intervention condition schools over two weeks by trained educators. During this period, wait-list control condition schools will continue usual classroom activities. Following the intervention phase, all students will complete a post-intervention survey (one week after the intervention), followed by a third 12-week follow-up survey to assess longer-term intervention effects. All surveys will be completed by pencil and paper, or online using Qualtrics (online survey software) depending on the school’s preference. Researchers, usual classroom teachers, learning support staff, and usual school volunteers will assist children to complete the surveys (e.g., assist with reading survey items or clarifying instructions). Surveys will take approximately 30 min to complete. Teachers in participating classrooms in intervention condition schools will complete a program evaluation survey at the post-intervention and 12-week follow-up timepoints. Figure 1 presents the flow of the participants in the trial.

Students in the wait list control condition will receive the Thriving Minds program following the completion of the 12-week follow-up survey. After the final survey, semi-structured interviews (30–60 min) will also be conducted in intervention condition schools with staff members who are best placed to provide qualitative insights into cultural changes in the classroom and school and attitudinal or behavioural changes in the students who received the intervention. Focus groups (30–45 min) will also be conducted with children to explore their perspectives on the program. Clinical support will be provided if a participant becomes distressed while completing trial surveys or focus groups.

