### Intervention

All students will receive the Thriving Minds program, either after the first survey (intervention condition), or after the third survey (wait-list control condition). The Thriving Minds program is conducted over two 50-minute sessions, delivered one week apart. The program aims to address mental health literacy and stigma by normalising uncomfortable emotional experiences, equipping students with effective self-care strategies, and encouraging them to seek help for emotional problems. Content is mapped to the Australian curriculum and delivered with classroom teachers present, who are ideally placed to support ongoing classroom use of emotion literacy content [27]. The program sessions focus on key concerns for 8–10-year-olds, including coping with stress/anxiety and low mood. The content is delivered through developmentally appropriate story books relating to anxiety and depression and classroom discussions and activities relating to the development of emotion literacy. Specifically, content focuses on recognition of emotional experiences (identification of different emotion characteristics, including physiological characteristics, distinguishing between comfortable and uncomfortable and big and small emotions), knowledge about appropriate regulation actions (self-care strategies), and help-seeking for uncomfortable emotions. A summary of the program content is included in the Supplementary Materials A.

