#### Help-seeking

The primary outcome for the current trial is *Help-seeking intentions* and will be assessed using the General Help-Seeking Questionnaire [GHSQ] [28]. Participants will be asked to rate how likely they are to seek help for big uncomfortable emotions from a range of people, including a friend, teacher, parent, family member, psychologist or school counsellor, doctor, and Kids Helpline (phone helpline). Participants will be provided with the opportunity to nominate another person (‘Other’) if they want to. All items will be responded to on a 5-point scale ranging from 1 (Extremely unlikely) to 5 (Extremely likely). Participant *help-seeking knowledge* will be measured by asking children to provide a free text response to indicate who they would get help from if they were having uncomfortable emotions (adapted to an open-ended question from a multi-choice response item on the GHSQ [28]). Total informal (e.g., family, friends, teacher) and formal (e.g., GP, psychologist, helpline) sources of help will be calculated.

Participant *help-seeking confidence* will be measured with a single item asking children to indicate on a 5-point scale ranging from 0 (Not at all) to 4 (Extremely) how easy it is for them to seek help. This item is adapted from a previous study [29], with the term ‘easy’ replacing ‘confidence’ to align with developmental literacy levels.

Participant *help-seeking attitudes* will be measured by asking children to rate how helpful each of 12 actions are for when they have *big, uncomfortable emotions*, using a 5-point rating scale ranging from 1 (very unhelpful) to 5 (very helpful), adapted from [30]. The list includes *no action* options (e.g., ‘Pretend the emotions aren’t there’), *self-help* actions aligning with the content of the Thriving Minds program (e.g., ‘Do something to make myself feel better (self-care)’), *informal help-seeking* actions (e.g., ‘Talk to a parent’) and *formal help-seeking* actions (e.g., ‘Talk to a psychologist or school counsellor’). Each individual response item will receive a helpfulness rating, and average scores across no action, self-help, informal help-seeking and formal help-seeking will also be calculated.

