#### School support

School support will be measured using two scales originally from the Sources of Strength trials [39, 40], adapted with minor language modifications. Four items will be used to assess *peer integration* at school, addressing both inclusion and isolation. Participants will respond to each item on a 4-point scale ranging from 1 (Strongly disagree) to 4 (Strongly agree). A mean scale score is calculated. Higher scores reflect higher peer integration. *Trusted adults at school* will be measured using a 4-item scale, α = 0.90 [41] on which participants rate their connections to adults at school on a 4-point scale ranging from 1 (strongly disagree) to 4 (strongly agree). A mean scale score is calculated, with higher scores indicative of students having adults at school that they feel they can trust and talk to about problems.

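### Class teachers may help children answer the outcome surveys, and after baseline only intervention-arm teachers have sat in on the program

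*Protocol article*

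**What the plan says.** Five statements in the protocol article bear on this point.

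- **Who helps.** Procedure: "Researchers, usual classroom teachers, learning support staff, and usual school volunteers will assist children to complete the surveys". The help is illustrated as "e.g., assist with reading survey items or clarifying instructions". These are examples rather than limits, and nothing separates the arms or the three survey occasions.
- **Who has seen the program.** Intervention: content is "delivered with classroom teachers present, who are ideally placed to support ongoing classroom use of emotion literacy content". For controls, Procedure says: "Students in the wait list control condition will receive the Thriving Minds program following the completion of the 12-week follow-up survey".
- **What is measured.** Help-seeking: "The primary outcome for the current trial is *Help-seeking intentions* and will be assessed using the General Help-Seeking Questionnaire". The child rates the likelihood of seeking help "from a range of people, including a friend, teacher, parent, family member, psychologist or school counsellor, doctor, and Kids Helpline".
- **Shared vocabulary.** Intervention says the sessions teach children to tell comfortable from uncomfortable and big from small emotions, to recognise bodily signs, and to seek help. The Help-seeking items ask about emotions that are both big and uncomfortable. Emotion Knowledge asks children to classify emotions on the same two pairs, and its vignettes and bodily-feeling items were written to match program content.
- **Blinding.** The only blinding stated, in the Data analysis plan, applies to researchers who enter written surveys.

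**The concern.** An 8- to 10-year-old who is unsure of an item will ask the adult who is helping. If that adult is the class teacher, the reply after baseline comes from different positions in the two arms. An intervention teacher has heard the program's definitions and its advice to seek help, and is expected to keep using them in class. A control teacher has not.

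An explanation or nudge of that kind would be counted as a program effect on the primary outcome, or on the secondary emotion-recognition and bodily-sign outcomes. Because the difference arises after the baseline survey, comparing change from baseline does not remove it. Allocation is already non-randomised (Condition allocation), which is a further reason not to leave an avoidable difference in how outcomes are collected.

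**Working it through.** The plan states no figure on this point. The check is therefore to set the sections side by side, followed by one calculation for scale.

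**Helper's exposure at each survey**

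| Survey | Intervention-arm class teacher | Control-arm class teacher |
|---|---|---|
| Pre-intervention | not yet exposed through the trial | not yet exposed through the trial |
| Post-intervention | present at the sessions | not exposed |
| 12-week follow-up | present, and expected to support continued use | not exposed |

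The first row is symmetric and the other two are not. The hypothesis test concerns the second row (Aims and hypotheses).

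**Does a stated safeguard close the gap?** Blinded entry acts after the child has answered, and only on written surveys; Procedure also allows online completion. It cannot alter what was said while the child was answering.

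**Scale (the bias is assumed, not estimated).** Inputs from Participants and recruitment: about 500 children, 12 schools, 20% attrition, intraclass correlation 0.03.

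1. Analysed: 500 × 0.8 = 400, that is 200 per arm and 400/12 = 33.3 per school.
2. Design effect: 1 + (33.3 − 1) × 0.03 = 1.97.
3. Effective number per arm: 200/1.97 = 101.5.
4. Standard error of the difference in SD units: √(2/101.5) = 0.140.
5. With no true effect and a between-arm reporting shift b, the two-sided 5% test rejects with probability 1 − Φ(1.96 − b/0.140) + Φ(−1.96 − b/0.140).

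| Assumed b (SD) | Rejection rate |
|---|---|
| 0 | 5% |
| 0.05 | 6.5% |
| 0.10 | 11% |
| 0.15 | 19% |
| 0.20 | 30% |

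The formula gives the same rate for a shift of either sign. A shift against the program would mask a benefit instead of creating one. The calculation uses a normal reference, equal school sizes and no baseline adjustment. It shows sensitivity and is not a forecast.

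**The case against.** The case against has real force.

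- **The help is modest.** The only examples given are neutral: reading items and clarifying instructions. Researchers also help. Patient and public involvement reports that children of this age trialled the measures, which were then adjusted for clarity, so fewer questions should arise. This stands and limits the likely size. It does not remove the asymmetry, because the examples set no boundary.
- **Social desirability is mostly shared.** A reader might infer that rating the teacher in front of a teacher inflates scores in the intervention arm only. The documents do not support that. Teachers help in both arms and at baseline, and the item is one generic source among seven named ones, not a rating of the helper. Only help informed by the program differs by condition.
- **Control teachers are not ignorant.** A reader might suppose that only intervention teachers could prompt a right answer. Any teacher could do so for a child left out of a party. The difference lies in the program's terms and message.
- **Trusted adults at school.** It is tempting to add this scale, but Aims and hypotheses lists school support among exploratory predictors and mediators, not as a primary or secondary outcome.
- **Size and direction.** A reader might express the bias as a share of the anticipated d = 0.35, or take it to favour the program. The documents give no bias to put in the numerator, and that effect size is anticipated for literacy and stigma, not for help-seeking intentions. A favourable direction is plausible but not shown.
- **Article format.** A survey-administration script may exist in a fuller protocol, so its absence here is not a finding. The stated choice of helper remains.
- **Residual bias.** Children know whether they had the program, and researchers are not said to be blind when administering surveys. Changing the helper reduces one source of bias but does not blind the outcome.

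**Conclusion.** The point holds as a modest risk of condition-specific prompting at the two post-baseline surveys. It follows from three stated facts: class teachers help with self-report surveys, they attend the sessions in intervention schools, and control schools receive the program only after the last survey. Blinded data entry does not address it. No error or internal contradiction is shown, and nothing in the document says that bias has occurred.

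Its size and direction are unknown, and the rejection rates above depend entirely on the assumed shift. The conclusion rests on two assumptions: that some children ask about item meaning and not only about the response format, and that some class teachers answer. Both are plausible at this age, and the document neither confirms nor excludes them.

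**What to change.** Amend the Procedure section so that the same rules apply in both conditions and at all three surveys:

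1. Items are read aloud word for word.
2. Clarification is limited to how to mark an answer, with no definitions, examples or program terms.
3. Class teachers supervise the room, may read verbatim, and do not view or discuss answers.
4. One-to-one help on the help-seeking intentions questionnaire and the emotion-knowledge items comes, where possible, from researchers or other listed helpers who did not attend the sessions. The article does not say whether learning support staff or volunteers attend, so this has to be checked school by school.
5. Each survey records whether one-to-one help was given and by which type of helper.

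Data collection was planned for Terms 3 and 4 of 2023 and Terms 1 and 2 of 2024, and the article appeared in April 2024, so some surveys may already be complete. For those, the trial report should state who assisted in each arm, as far as that can be established.

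The cost is a short instruction sheet, one tick-box per survey, reassignment of people already named, and somewhat slower administration. The burden is greatest where many of the 40 to 50 children in a school need individual help during a survey of about 30 minutes.
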